### Study procedures

#### Instruction of healthcare providers

All healthcare providers are well informed about the study procedures in three, 2-hour meetings with the research group. They are explicitly instructed not to talk about randomization and allocation to their patients. Written information is provided as well.

#### Baseline assessment

Baseline parameters include socio-demographic and anthropometric parameters, MRC dyspnoea scale, HADS, SGRQ, the self-efficacy questionnaire and lung function values. Medical records are checked for the presence of lung function assessment in the previous three months. If absent, spirometry is scheduled before inclusion. Post-bronchodilator Forced Expiratory Volume in one second (FEV_1_), Forced Vital Capacity (FVC) and FEV1/FVC ratio are assessed.

#### Follow-up assessment

Patients are instructed to record any increase in a predetermined list of symptoms over their chronic (stable) symptoms during the previous 24 hours. Every third day the CCQ is completed. Patients receive six diary booklets, each consisting of 30 days. After completing one of the diaries, patients are asked to send them to the investigator. Every four weeks patients are contacted by telephone to assess healthcare utilization and to evaluate proper use of the diary. At 24 weeks, HRQL, anxiety and depression, dyspnoea and self-efficacy are reassessed. After filling in the last diary and follow-up questionnaire, patients receive a postponed-information letter about the aim of the study and AP and their allocation. Additional data regarding health care consumption (exact date and content of visits and interventions) are obtained from medical records.

### Sample size

Based on two studies, a median health status recovery time around 12 (IQR 8-16) days is expected [9,27]. Unfortunately we do not know the shape of the underlying distribution. Nevertheless, a nonparametric test might require either more or fewer subjects compared to a Students' t-test, but they never require more than 15% additional subjects if 1) the number of subjects is reasonably high: (how high depends on the nature of the distribution and test, but figure at least a few dozen) and 2) the distribution of the data is not unusual (does not have infinite tails, in which case its standard deviation would be infinitely large)[28].

Hence, we adopted the general rule for computing the sample size required for a t-test. In a normal distribution the distance between the first quartile and the median is approximately 0.67 times the standard deviation of the distribution. Thus, if we assume the distribution of recovery time (median = 12, IQR = 8-16) to be normal, the mean of this distribution will be 12, with standard deviation 6. Sample size is calculated based on the smallest detectable change of one 3-day CCQ unit. Using the aforementioned 15%-rule, would mean a sample size of 63 (two tailed t-test) * 1.15 (+ 15%) = 73 exacerbations are needed in both arms to have an 80% chance of detecting a difference, using a two side alpha = 0.05.

### Data analysis

SPSS 15.0 for Windows (SPSS, Inc., Chicago, IL) will be used for data analysis. Baseline characteristics are expressed as means and standard deviation or medians and interquartile range. All data will be analysed as intention to treat. Differences in CCQ symptom recovery time between both groups will be evaluated using Mann-Whitney *U *test. Number of exacerbations will be reported as weighted exacerbations rates (total number of exacerbations divided by the total person-time of follow up per group). This approach has shown to produce unbiased estimates of a weighted statistical approach adjusted for asymmetry in follow-up times by accounting for each patient's time spent in the trial [31,32]. Statistical significance of weighted rate ratio's are calculated using a Poisson regression model including an overdispersion parameter to account for variability in exacerbation rates between patients. Other variables will be analyzed using paired student t-test (continuous data), chi-square test (binominal data) and Mann-Whitney *U *test (ordinal data). To determine the magnitude of the treatment effect, Cohen's effect sizes are calculated for continuous variables measuring differences in pre- and post-change.

Confidence intervals of the incremental cost-effectiveness ratio's are tested using nonparametric bootstrapping (Monte - Carlo simulation) drawing 100.000 samples[33].

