**Methods/Design:**

The current multicenter, single-blind RCT with a follow-up period of 6 months, evaluates the hypothesis that individualized AP's reduce exacerbation recovery time. Patients are included from regular respiratory nurse clinics and allocated to either usual care or the AP intervention. The AP provides individualized treatment prescriptions (pharmaceutical and non-pharmaceutical) related to a color coded symptom status (reinforcement at 1 and 4 months). Although usually not possible in self-management trials, we ensured blinding of patients, using a modified informed consent procedure in which patients give consent to postponed information. Exacerbations in both study arms are defined using the Anthonisen symptom diary-card algorithm. The Clinical COPD Questionnaire (CCQ) is assessed every 3-days. CCQ-recovery time of an exacerbation is the primary study outcome. Additionally, healthcare utilization, anxiety, depression, treatment delay, and self-efficacy are assessed at baseline and 6 months. We aim at including 245 COPD patients from 7 hospitals and 5 general practices to capture the a-priori sample size of at least 73 exacerbations per study arm.

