### Outcomes and measurements

#### Exacerbations

Exacerbations are detected by daily recording of symptoms. Symptoms recorded are termed major and minor (figure 2) according to Anthonisen et al[20]. A symptom-based exacerbation is defined by the onset of two or more new or deteriorated symptoms, of which at least one major symptom, persisting for 48 hours or more. A subsequent exacerbation is defined as a new event only in the presence of at least two stable weeks. Exacerbation onset is defined by the first day on which the symptom criteria are met. Daily symptoms are binary coded and summed to give a daily symptom count. Major are scored as: normal = 0; small increase = 1; or clear increase = 2. The minor symptoms are scored 0 and 1 respectively. Adding all these scores results in a daily symptom count with a range from 0-11 points. Exacerbations are recovered when the three-day moving mean of the symptom count returns to the symptom count of days fourteen to eight prior to exacerbation onset.

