Finally, the current study clearly differs from the other studies in the primary outcome on which the study is powered. Aiming at evaluating effectiveness of a single component intervention (AP) necessitates being reserved on powering on general outcome measures such as hospital admissions. Therefore, the current study aims at specific and accurate assessment of effectiveness of the AP on patient-centred outcomes, in the presence of an exacerbation, since this is what the AP is developed for. In addition, a clinical relevant advantage of assessing exacerbation recovery time is that it assesses effectiveness in all exacerbation episodes and not only those followed by healthcare contacts or hospital admissions. Effectiveness in terms of decreased CCQ recovery time is equivalent to a decrease in the impact of these episodes on health status and thus highly clinical relevant from a patient perspective. Detecting an effect on recovery time of exacerbations, the primary outcome, is an essential first step before trying to prove that the intervention can increase HRQL or reduce hospital admissions. In conclusion, this RCT identifies whether an AP is an effective component of self-management in patients with COPD and clearly differentiates from existing studies in its design, outcome measures and robustness.

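### The primary Mann-Whitney U test is worded per exacerbation without limiting each patient to one episode or allowing for clustering, so its 5% error rate and 80% power are secured only for one episode per patient

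*Protocol article*

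**What the plan says.** - **Unit of randomisation.** The Design section assigns individual patients 1:1, and Table 1 lists the randomisation as individual.
- **Unit of outcome.** The Abstract states: "CCQ-recovery time of an exacerbation is the primary study outcome".
- **Unit of sample size.** The Sample size section concludes that "73 exacerbations are needed in both arms to have an 80% chance of detecting a difference". It assumes that "the mean of this distribution will be 12, with standard deviation 6" and takes as its target the "smallest detectable change of one 3-day CCQ unit".
- **Repeat episodes.** The Exacerbations section provides for them: "A subsequent exacerbation is defined as a new event only in the presence of at least two stable weeks".
- **Test.** The Data analysis section says: "Differences in CCQ symptom recovery time between both groups will be evaluated using Mann-Whitney" U test. I read this as the primary CCQ recovery outcome. No other test is named for it.
- **Between-patient variability.** It is mentioned only for exacerbation rates, through an overdispersion parameter in a Poisson model.

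No section restricts the recovery-time comparison to one episode per patient, summarises episodes within patient, or adjusts for clustering.

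**The concern.** The Mann-Whitney U test requires independent observations. Two recovery times from the same patient share that patient's disease severity, care and way of completing the diary, so some positive correlation is plausible. If several episodes per patient enter the test as if they were separate patients, the standard error is too small and frequent exacerbators carry more weight than others. The p-value at stake is that of the primary comparison.

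This goes beyond detail that an article may leave to a fuller document. The article itself fixes both a unit (the exacerbation) and a test (one for independent observations), and the two fit together only under a restriction that it does not state. The Discussion also faults two earlier cluster-randomised trials for not enlarging their samples for clustering; the same principle applies to episodes within patients.

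**Working it through.** **1. The plan's own figures**

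Inputs (Sample size section): difference 3 days, SD 6 days, two-sided alpha 0.05, power 80%, plus 15% for the nonparametric test.

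- n per arm = 2 x (1.960 + 0.842)^2 x (6/3)^2 = 62.8, rounded up to 63.
- 63 x 1.15 = 72.45, rounded up to 73.

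Both figures reproduce. The formula assumes independent observations.

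**2. What the 146 counts**

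Inputs: 70% of patients with an exacerbation in 6 months, 15% loss, 60% response.

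- 146 / 0.70 = 208.6; / 0.85 = 245.4; / 0.60 = 409.0.
- Forwards: 245 x 0.85 x 0.70 = 145.8, or 73 per arm.

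This reproduces the 409, and the 245 of the Abstract and Table 1. (The 282 in the Sample size section does not follow from its inputs, since 409 x 0.60 = 245; that is a separate matter.) Because 70% is a proportion of patients, 146 is a number of patients, although the text calls it exacerbations.

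**3. How many episodes to expect**

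Cited rates run from 2.53 to 5.0 per patient-year.

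- Per patient in 6 months: 2.53/2 = 1.265 to 5.0/2 = 2.5.
- In about 208 completers: 208 x 1.265 = 263 to 208 x 2.5 = 520 episodes, against the 146 stated.
- Share with two or more episodes, assuming Poisson counts, 1 - exp(-m)(1 + m): 36% at m = 1.265 and 71% at m = 2.5.

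**4. Type I error if all episodes are pooled**

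The article gives no ICC, so 0 to 0.5 is an assumed range. Simulation with no treatment effect: 104 completers per arm, mean 12 and SD 6 days, a normal patient effect, 4000 trials per setting, and 1.27, 1.75 or 2.5 episodes per patient. Counts were Poisson, overdispersed with k = 2, or (in a separate simulation) overdispersed with shape 3.2. The last value matches the cited 3.5 ± 2.7 per year: 3.5^2 / (2.7^2 - 3.5) = 3.2.

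Design effect (DE) = 1 + (m_w - 1) x ICC, where m_w is the size-weighted mean number of episodes per patient: 2.25 to 3.49 for Poisson counts.

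| ICC (assumed) | Type I error, Poisson | Type I error, k = 2 | Type I error, shape 3.2 | DE, Poisson | 73 x DE |
|---|---|---|---|---|---|
| 0 | 4.2-5.1% | 4.6-5.1% | 5.2-5.5% | 1.00 | 73 |
| 0.1 | 5.8-8.0% | 8.0-8.6% | 6-9% | 1.13-1.25 | 83-92 |
| 0.3 | 8.7-13.7% | 11.9-16.5% | 10-17% | 1.38-1.75 | 101-128 |
| 0.5 | 12.0-17.4% | 14.7-23.8% | 15-22% | 1.63-2.25 | 119-164 |

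If only about 73 episodes per arm were collected, from fewer patients, type I error would be 7-8%, 10-13% and 12-20% at ICC 0.1, 0.3 and 0.5.

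**5. One episode per patient**

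With at most one episode per patient (ICC 0.3 setting), simulated type I error is 5.0%, and 73 per arm stands.

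**The case against.** A reader might infer that the plan definitely pools repeat episodes, and so that the 5% level definitely fails. The documents do not prove this.

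- The Discussion says of the outcome that "it assesses effectiveness in all exacerbation episodes and not only those followed by healthcare contacts or hospital admissions". The contrast there is between reported and unreported episodes, not between first and later ones.
- The rule for a subsequent exacerbation is needed anyway for the secondary outcomes counted per patient-year. It does not say that repeats enter the recovery-time test.
- The conversion in step 2 uses one episode per patient, and the 15% allowance is expressed in subjects. The only arithmetic given therefore fits independent observations, and on that reading the test is valid.
- The inflation depends on an ICC that the article does not give. Recovery is judged against the patient's own earlier CCQ level, which could remove some stable differences between patients and lower the correlation.
- The article is condensed, and a fuller document may name the episode to be analysed.

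These points stand as limits on certainty. They do not remove the concern. The outcome, the 73 and the 146 are all worded as exacerbations, the literal reading of the test is over exacerbations, and no section says that one episode per patient is used or which one. If one was intended, the unit of the primary analysis is still not fixed, and the choice remains open after the data are seen.

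**Conclusion.** The plan needs correcting. Read literally, a test for independent observations is applied to exacerbations that can cluster within patients. If all episodes enter, type I error exceeds 5% for any positive within-patient correlation: roughly 6-9%, 9-17% and 12-24% at assumed ICCs of 0.1, 0.3 and 0.5. At ICC 0, or with one episode per patient, the level holds. Pooling is the natural reading of the wording but is not established.

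The 146 is mislabelled, and the stated 80% power applies only to one episode per patient. It should not be inferred that the trial is therefore too small. With Poisson counts, pooling would supply about 132 to 260 episodes per arm (104 x 1.265 and 104 x 2.5), which exceeds the 119 to 164 needed at ICC 0.5. The fault lies in the validity of the naive test and in what the stated power refers to.

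**What to change.** Choose one of two routes and state it before the data are analysed.

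1. **First exacerbation per patient as primary.** State that the primary Mann-Whitney U test uses each patient's first symptom-based exacerbation, with a patient-clustered analysis of all episodes as supportive. This matches the existing conversion and keeps 73 per arm valid. Cost: later episodes are left out of the primary test.
2. **All episodes as primary.** Replace the plain test with a patient-clustered method, such as a rank-sum test for clustered data, and restate the power with a design effect under a stated ICC. Cost: wider intervals than the naive test would give, and a new power statement. Under Poisson counts the planned 245 patients would suffice over the ICC range shown. With overdispersed counts (k = 2, m_w = 2.87), the lowest rate and ICC 0.5, the need is 73 x (1 + 1.87 x 0.5) = 142 per arm against about 132 expected, a small shortfall.

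Under either route, relabel the 146 as patients with at least one exacerbation (73 per arm). The first route changes wording only; neither needs new kinds of data.

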### Secondary objectives

To evaluate effectiveness of an individualized Action Plan on in the event of an exacerbation on, symptom recovery time (days), treatment delay, healthcare utilisation, health-related quality of life (HRQL), depression and anxiety and self-efficacy.

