## Methods

### Design

The study is conducted as a single-blind randomised controlled trial, with a 6 months follow-up. Patients are randomly assigned to either care as usual or treatment with an individualized AP as an addition to care as usual. The randomisation procedure is performed by a respiratory nurse (RN). To conceal the assignment sequence, a central web-based service on a 1:1 basis is used. Randomisation is stratified by centre and gender.

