##### Health-related quality of life

The St George Respiratory Questionnaire (SGRQ) is used to measure health-related quality of life (HRQL). It is validated for measuring health impairment in COPD patients. The SGRQ consists of sixteen questions in three domains: symptoms, activity and impact. It assesses patients' perception of respiratory problems over a preceding period, ranging from one month to one year, as well as their current state[23]. Both between group differences in SGRQ scores will be assessed as well as the proportion of patients crossing the clinical relevant threshold of 4 points [24].

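### The test named for continuous secondary outcomes, a paired t-test, measures change over time within patients and does not compare the Action Plan with usual care

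*Protocol article*

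**What the plan says.** The Data analysis section deals first with recovery time (Mann-Whitney U between the groups) and exacerbation rates (Poisson regression with an overdispersion parameter). It then covers everything else in one sentence: "Other variables will be analyzed using paired student t-test (continuous data), chi-square test (binominal data", with Mann-Whitney U for ordinal data. No independent-samples t-test, ANCOVA or mixed model is named for continuous data. The next sentence adds that "Cohen's effect sizes are calculated for continuous variables measuring differences in pre- and post-change", as a measure of the size of the treatment effect.

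Three other places bear on this:

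- **Design:** "Patients are randomly assigned to either care as usual or treatment with an individualized AP as an addition to care as usual", and "a central web-based service on a 1:1 basis is used". Stratification is by centre and gender.
- **Secondary objectives:** effectiveness of the Action Plan is to be evaluated on "symptom recovery time (days), treatment delay, healthcare utilisation, health-related quality of life (HRQL), depression and anxiety and self-efficacy".
- **Health-related quality of life:** "Both between group differences in SGRQ scores will be assessed as well as the proportion of patients crossing the clinical relevant threshold of 4 points".

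On timing, the Follow-up assessment section says: "At 24 weeks, HRQL, anxiety and depression, dyspnoea and self-efficacy are reassessed". The Baseline assessment section lists the SGRQ, HADS and self-efficacy questionnaire among the measures taken at entry.

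**The concern.** A paired t-test needs pairs. There are none across the arms, because patients were randomised individually and not matched. The only pairing the data offer is baseline against 24 weeks in the same patient. That comparison can be run in one arm, in each arm separately or in all patients pooled, and in none of these forms does it contain a treatment contrast.

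Change shared by both arms is likely here. Patients enter over five months in winter and spring and are followed for six months, and every patient in either arm has a systematic review by a respiratory nurse at inclusion. A paired test registers such shared change as a finding. If the sentence is followed literally, a statement about the Action Plan's effect on the SGRQ score, or on HADS and self-efficacy scores where these count as continuous, would not rest on the randomised comparison.

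For continuous outcomes with no baseline value, the named test cannot be run at all. Treatment delay, for example, is defined only once an exacerbation has begun.

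**Working it through.** **1. Which t-test the article uses elsewhere.** The Sample size section takes SD 6 days, difference 3 days (one CCQ unit), two-sided alpha 0.05 and power 80%.

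- Independent two-sample test, normal approximation: n = 2 × (1.96 + 0.84)² × 6² / 3² = 62.8, so 63 per arm, as stated. The t-distribution gives 63.8.
- Inflation: 63 × 1.15 = 72.45, so 73 per arm, as stated.
- A paired or one-sample t-test at the same standardised effect (3/6 = 0.5) would need 33.4, so 34 pairs.

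The sample size therefore reproduces, and it comes from an independent-groups test. The paired test appears only in the sentence on the remaining variables.

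**2. What each data type receives in the Data analysis section.**

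| Outcome | Named test | Compares the arms? |
|---|---|---|
| CCQ recovery time (primary) | Mann-Whitney U | Yes |
| Exacerbation rates | Poisson, overdispersed | Yes |
| Binary, e.g. share of patients passing the SGRQ threshold | Chi-square | Yes |
| Ordinal | Mann-Whitney U | Yes |
| Continuous, baseline and 24 weeks (SGRQ score; HADS and self-efficacy if continuous) | Paired t-test | No |
| Continuous, no baseline (e.g. treatment delay, unfavourable health status days, hospital days, if continuous) | Paired t-test | Cannot be applied |

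The fifth row contradicts the promise in the quality-of-life section: "Both between group differences in SGRQ scores will be assessed".

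**3. What the paired test picks up when the Action Plan does nothing.** Assumptions, none of them stated in the article: 245 × 0.85 / 2 = 104 completers per arm (using its 245 patients and 15% loss), normally distributed change with SD 1, and the same true mean change in both arms. Simulation of 20,000 trials per row:

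| Shared change (SD) | Paired test significant in Action Plan arm | Independent-samples test on change significant |
|---|---|---|
| 0 | 5.0% | 4.8% |
| 0.2 | 52% | 4.8% |
| 0.3 | 86% | 4.9% |
| 0.5 | 99.9% | 4.9% |

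The paired test is doing its own job correctly: it detects change over time. It is simply not a test of the Action Plan.

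**4. Precision of the replacement.** Let r be the correlation between baseline and 24-week score. The article gives none, so 0.7 is assumed, with range 0.5 to 0.8. Relative to the variance of the unadjusted follow-up score:

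- ANCOVA, 1 − r²: 1 − 0.49 = 0.51 (0.75 at r = 0.5; 0.36 at r = 0.8).
- Change score, 2(1 − r): 2 × 0.3 = 0.60 (1.00 at r = 0.5; 0.40 at r = 0.8).

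These figures bear on the choice of remedy. They do not measure the size of the error.

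**The case against.** The best defence is that paired is a slip. The objectives concern effectiveness, the SGRQ section promises a group comparison, the other tests in the same sentence are for independent groups, and the sample size rests on a two-sample t-test. An independent test on change scores may well be what was meant. This explanation is plausible, and it makes the correction easy. It does not remove the fault, because a reader or programmer following the sentence would run the wrong test and no other sentence overrides it.

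Three stronger readings are tempting, and the article does not support them.

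- **That the effect sizes share the fault.** A reader might infer that Cohen's effect size is to be computed from baseline-to-follow-up change within each arm. The article does not say so. Its wording fits a between-arm difference in change equally well, and on that reading seasonal change and regression to the mean are common to both arms and cancel in expectation. The sentence is ambiguous, not shown to be wrong. Either way, an effect size is not a test.
- **That the trial will conclude from significance in one arm and not the other.** With equal true change, exactly one arm is significant with probability 2p(1 − p), which is 50% at within-arm power p = 0.5 and 32% at p = 0.8. The arithmetic is right, but the plan states no such decision rule and gives no such powers.
- **That all conclusions on quality of life, mood and self-efficacy fail.** The proportion crossing the SGRQ threshold goes to chi-square. HADS has score categories and self-efficacy is built from Likert items, and the article does not say whether their totals count as continuous or ordinal. If ordinal, they already have Mann-Whitney U.

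**Conclusion.** The point holds in a limited form. The article assigns continuous secondary outcomes a test that cannot compare the randomised arms, and this contradicts its own stated comparison. Because a specific test is named and is unsuitable, this is an error in the text and not detail left to a fuller plan.

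Its reach is the SGRQ score, HADS and self-efficacy scores if treated as continuous, and any continuous outcome without a baseline. The primary analysis, exacerbation rates, binary and ordinal outcomes and the sample size are untouched.

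The rates of 52% to 99.9% against about 5% show how far the two tests can diverge when there is no treatment effect. They depend on the assumed shared change of 0.2 to 0.5 SD and 104 completers per arm, and they are an illustration, not a forecast for this trial. That the paired test lacks a treatment contrast depends on no assumption.

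**What to change.** Replace the paired t-test with between-arm analyses, and clarify the effect size:

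- **Continuous outcomes with a baseline value:** ANCOVA of the 24-week score on arm, baseline score, centre and gender, reporting the adjusted between-arm difference with its 95% confidence interval. An independent-samples t-test on change would also remove the error. ANCOVA is preferred for precision and because it takes in the stratification factors.
- **Continuous outcomes without a baseline value** (for example treatment delay, unfavourable health status days, hospital days): an independent-groups comparison, since adjustment for baseline is impossible.
- **Data type:** say whether HADS and self-efficacy totals are analysed as continuous or ordinal.
- **Cohen's effect size:** state that it is computed from the between-arm difference.

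The cost is a few sentences in the Data analysis section. The baseline scores are already collected, and no sample size, visit or measurement changes.

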##### Health care utilization and cost-effectiveness

The number of respiratory-related hospital admissions, hospital days, emergency room visits and scheduled and unscheduled visits or telephone calls to both respiratory and family physicians are assessed. The proportion of patients having one or more respiratory-related hospital admissions is determined, as well as the number of days between inclusion and first hospital admission.

The perspective of the healthcare payer is adopted for the cost-effectiveness analysis (CEA). Resource use is valued in monetary terms by multiplying the units consumed by the cost per unit[26]. Two major cost categories are distinguished: program implementation and direct health care. Data on cost and outcome are brought together to estimate incremental cost-effectiveness ratios (ICERs) and subsequently calculated as costs per exacerbation-related CCQ unit prevented, per hospital admission prevented, and per health care contact prevented. Sensitivity analysis is used to test the cost-effectiveness model for methodological uncertainty and generalizability.

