***Statistics***				
Follow-up (mths)	6	6	12	12
n		56	102	151
Powered on	Δ exa-rt = 1	Δ SGRQ = 5.7	Δ SGRQ = 4	Δ SGRQ = 4
SSC	245	124	124	160

OC, outpatient clinic; GP, general practice; exa-rt, exacerbation recovery time; SGRQ, St George respiratory questionnaire n, number of patients; SSC, sample size calculation; pt, patient; inv, investigator.

Usually, blinding in self-management or educational interventions is nearly impossible, but the so called 'modified informed consent' procedure, does enable a single-blind RCT and consequently compensates for substantial threats to internal validity. In the field of disease management research this can be regarded innovative in terms of methodology.

In the studies of Wood-Baker et al[34] and McGeoch et al[35], randomization was clustered to prevent cross-contamination of educational messages within a practice. Selection bias in cluster randomized trials may threaten the validity of the results. These studies however did not inflate their sample size to accommodate for this clustering effect [36]. We believe that in this robust study (245 patients) the impact of contamination is regulated by the modified informed consent procedure (patient not knowing that the AP is part of the study objective) and the strict instructions of RN's not to inform control patients about the existence of the AP. The remaining threat of contamination does not weigh against the disadvantage of the huge sample size needed in a clustered trial to compensate for the high inter-cluster variations in both patient (i.e socioecomic differences) and healthcare (i.e. number and content of respiratory nurse consultations) characteristics.

Although all studies used an individualized AP, aimed at early recognition of exacerbations, there are some differences between the interventions. Instead of encouraging self-initiation of antibiotics or oral corticosteroids, the AP used in the current study aims at early contact with a healthcare provider only. The choice to initiate pharmaceutical treatment is left to the physician. Moreover, we have respiratory nurses to evaluate use of the AP and provide additional information when needed. Reinforcement has shown to be essential in changing self-management behaviour, leading to better use of the intervention [37].

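### Bootstrap intervals are planned on the cost-effectiveness ratios themselves; for cost per admission prevented, and plausibly per contact prevented, a percentile interval is likely to be unreadable

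*Protocol article*

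**What the plan says.** The section on health care utilization and cost-effectiveness defines three incremental cost-effectiveness ratios (ICERs): "costs per exacerbation-related CCQ unit prevented, per hospital admission prevented, and per health care contact prevented". The Data analysis section then fixes how their uncertainty is expressed: "Confidence intervals of the incremental cost-effectiveness ratio's are tested using nonparametric bootstrapping", with 100,000 samples. The only other uncertainty analysis named is this: "Sensitivity analysis is used to test the cost-effectiveness model for methodological uncertainty and generalizability".

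The Sample size section powers the trial on recovery time alone: "Sample size is calculated based on the smallest detectable change of one 3-day CCQ unit", with enough exacerbations "to have an 80% chance of detecting a difference, using a two side alpha = 0.05". The Discussion says that the authors hold back from powering on general outcomes such as hospital admissions. It also says that the Action Plan "aims at early contact with a healthcare provider only", in contrast to plans that let patients start drugs themselves.

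**The concern.** An ICER is a cost difference divided by an effect difference. If the effect difference can plausibly be positive or negative, the sampling distribution of the ratio passes through infinity and its sign loses its meaning. A negative ratio can mean cheaper and better, or dearer and worse. A positive ratio can mean dearer and better, or cheaper and worse. Sorting the pooled ratios and taking percentiles puts these opposite conclusions side by side, and more replicates reduce only the Monte Carlo error.

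Two of the three denominators are candidates for this. Admissions are by the authors' own account not what the trial is sized for. Contacts are what the intervention is designed to bring forward, so whether any are prevented overall is open. What is at stake is the cost-effectiveness result on these two ratios. The primary comparison is not touched.

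**Working it through.** **The plan's own figures.** For a difference of 3 days, SD 6, two-sided alpha 0.05 and 80% power, n per arm = 2 × (1.96 + 0.8416)² × 6² / 3² = 62.8, so 63. Then 63 × 1.15 = 72.45, so 73 exacerbations per arm. Patients: 146 / (0.70 × 0.85) = 245.4, which matches the 245 in the Abstract. With 15% loss, 245 × 0.85 / 2 is about 104 per arm. (The Sample size section also prints 282 patients; with 15% loss that would be about 120 per arm. The result below at 122 per arm covers this.)

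**Formulas.** With effect difference d and standard error SE, the 95% interval spans zero with probability of about 1 − Φ(d/SE − 1.96). In a trial that observes exactly d, the share of bootstrap draws at or below zero is about Φ(−d/SE).

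**Ratio per CCQ unit** (recovery time as a stand-in, 73 per arm): SE = 6 × √(2/73) = 0.993.

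| True gain | d/SE | Interval spans zero | Draws ≤ 0 |
|---|---|---|---|
| 3 days | 3.02 | 14% | 0.1% |
| 2 days | 2.01 | 48% | 2% |
| 1.5 days | 1.51 | 67% | 7% |
| 1 day | 1.01 | 83% | 16% |

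At the nominal 80% power the first figure is 20%. Design effects of 1.2–1.5 for repeated exacerbations (assumed) give 21–31% at 3 days.

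**Ratio per admission.** The article states no admission rate, so control risk p and relative risk are assumptions, with admission treated as yes/no per patient. SE = √[p₁(1 − p₁)/104 + p₂(1 − p₂)/104].

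| Control risk | Relative risk | d | SE | Interval spans zero | Draws ≤ 0 |
|---|---|---|---|---|---|
| 5% | 0.8 | 0.010 | 0.0287 | 95% | 36% |
| 10% | 0.8 | 0.020 | 0.0397 | 93% | 31% |
| 10% | 0.7 | 0.030 | 0.0386 | 88% | 22% |
| 20% | 0.7 | 0.060 | 0.0519 | 79% | 12% |

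So the range is 79–95%. With 122 per arm (no loss) it is 76–94%. Even a relative risk of 0.5 leaves about 47–84% at 104 per arm.

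**Ratio per contact.** Also assumed: mean m of 2–4 contacts in 6 months, overdispersion φ of 2–4, rate ratio r of 0.8–0.9. SE = √[φ m (1 + r)/104].
- Most favourable case (m = 4, φ = 2, r = 0.8): d = 0.80, SE = 0.372, spans zero in 42%.
- Least favourable case (m = 2, φ = 4, r = 0.9): d = 0.20, SE = 0.382, spans zero in 92%.

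These figures already grant a true reduction of 10–20%.

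**What the ratio interval looks like.** Take 10% vs 7% admitted and an assumed cost difference of 100 with SE 150, independent of the effect. P(effect > 0) = 0.781 and P(cost > 0) = Φ(100/150) = 0.748. The quadrant shares are:
- dearer and better: 0.781 × 0.748 = 58%
- cheaper and better: 0.781 × 0.252 = 20%
- dearer and worse: 0.219 × 0.748 = 16%
- cheaper and worse: 0.219 × 0.252 = 6%

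About 36% of draws therefore give a negative ratio, and they carry two opposite meanings. The point ICER is 100/0.03 = 3,333. With 100,000 normal draws the 2.5 and 97.5 percentiles are about −42,000 and +46,000. Those limits do not bound any usable statement about cost per admission prevented.

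**The case against.** The strongest reply is that the article gives one sentence on the bootstrap, with a citation, and does not name the percentile method. Valid confidence sets for ratios exist, such as Fieller's, although they can be unbounded, and bootstrap replicates can also be ordered on the plane. A condensed article may leave a cost-effectiveness plane or acceptability curve to a fuller document, so their absence is no error. All of that stands. It narrows the criticism to a plain percentile interval on the ratio, but it does not remove it: the stated inferential product is an interval on the ICER, and a plane added elsewhere would not make that interval readable.

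Three stronger readings are tempting.
- A reader might infer that all three ratios fail because every effect difference will probably span zero. The documents do not support this. The ratio per CCQ unit sits closest to the powered outcome, and under the design assumptions the chance is about 14–20%. The match is approximate, since CCQ units prevented is not the same quantity as recovery time per exacerbation.
- A reader might infer that total contacts will rise. The Discussion speaks of early contact as opposed to self-started drugs, and earlier contact could avert later visits. The sign is uncertain, not shown to be adverse.
- A reader might infer that the economic conclusion hangs on these intervals. The article states no decision rule based on them, does not list cost-effectiveness among its objectives, and also plans a sensitivity analysis.

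**Conclusion.** The point holds for the ratio "per hospital admission prevented, and per health care contact prevented": likely for admissions, plausible for contacts. For admissions, the effect interval spans zero in about 79–95% of trials with assumed control risks of 5–20%, relative risks of 0.7–0.8 and 104 patients per arm. For contacts the corresponding range is 42–92%, on rates that are likewise assumed. The percentile limits in the worked example also depend on an assumed cost difference and its standard error; they illustrate the behaviour and do not predict the trial's result. No coverage probability of the planned interval was calculated.

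The ratio per CCQ unit is not condemned by this argument, although its exposure rises to 48% if the true gain is 2 days and to 83% if it is 1 day. The finding is a cheap improvement to a secondary analysis, not a threat to the trial's main conclusion.

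**What to change.** Keep the nonparametric bootstrap, resampling patients so that cost and effect stay paired. In place of a percentile interval on the ratio, base the uncertainty statement on:
- the cost difference and the effect difference, each with its own confidence interval;
- the replicates plotted on the cost-effectiveness plane;
- net monetary benefit, or an acceptability curve, over a willingness-to-pay range stated in advance.

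The point ICER can still be reported, read together with the plane. The change takes one or two sentences and uses the same replicates, with no extra data. The price is that no single ratio with an interval can be quoted, and a willingness-to-pay range has to be chosen for each effect measure.
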